**Figure 2 F2:**
[figure not shown]
The placement of electrodes on the dorsiflexor muscles of patient with hemiplegia.

During the stimulation, the participants will be instructed to remain in the supine position and relax. For the placebo group, electrodes will be placed at the same position as the active NMES condition; however, the current intensity will be gradually decreased after a few seconds to 0. Therefore, the participant will experience a passage of current on the muscle at the beginning but receive no current for the rest of the stimulation period. The participants will be informed that the stimulation is below the sensory level. After each visit, the participants would be investigated for any pain or skin irritation under the electrode. Adverse events would be listed and discussed with the participant. The pre- and post-training assessments will be completed within 3 days before and after the training sessions.

#### Sample Size Calculation

The sample size was calculated based on a previous study (7). However, considering a 10% attrition rate, the total sample size will be 44 participants. Each group had 22 participants.

### Statistical Analysis

IBM SPSS Version 25.0 (IBM Corp., Armonk, NY, USA) will be used to analyze the collected variables. The descriptive demographic information (means, medians, and SD) include age, gender, onset of the stroke, height, weight, and all outcome measures will be calculated and compared at the baseline using the independent *t*-test or chi-square test to ensure that there is no significant difference between the two groups at the baseline. Normality of the data will be assessed using the Shapiro–Wilk test. Comparisons between pre- and post-intervention will be conducted using the dependent *t*-test or the Wilcoxon signed rank test to determine if there will be significant differences between two different timepoints for each group. The independent *t*-test or the Mann–Whitney *U*-test will be used to compare the recorded values at the post-intervention between the two groups. In case of confounding variables such as age, secondary analysis will be performed according to the age groups (18–30, 31–50, and 51–65 years). In order to account for pre- and post-intervention between-group clinical effectiveness in terms of the outcome measures, Cohen's *d* effect size will be calculated. Furthermore, the pre-test effect sizes will be subtracted from the post-test effect sizes to effectively control for the differences at the baseline and obtain the absolute effect size. Effect sizes will be defined as small (*d* ≤ 0.2), medium (0.2 > *d* < 0.8), and large (*d* ≥ 0.8) (43). Differences will be considered statistically significant when *p* < 0.05.

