### Procedure

#### Assignment of Intervention

##### Allocation Sequence Generation

The participants will be randomly allocated at a 1:1 ratio into either EG (*n* = 22) or NMES_sham_ (*n* = 22). The randomization process will be generated by an independent research assistant who is not involved in the treatment or data collection using an online randomization website (https://www.graphpad.com/quickcalcs/randomize1.cfm).

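### Baseline significance tests at 22 per arm do not reliably show balance, and the plan's only response to confounding by age is an unspecified three-band analysis rather than a pre-specified adjusted model

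*Protocol article*

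**What the plan says.** All of the following is in the Statistical Analysis section of the protocol article unless another section is named.

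- **Baseline tests.** The variables "include age, gender, onset of the stroke, height, weight, and all outcome measures will be calculated and compared at the baseline" by independent t-test or chi-square test. The stated purpose is "to ensure that there is no significant difference between the two groups at the baseline".
- **Between-group test.** Post-intervention values are compared by independent t-test or Mann–Whitney U-test. No covariate is named.
- **Age.** Should a variable such as age confound, "secondary analysis will be performed according to the age groups (18–30, 31–50, and 51–65 years". The section does not say how a confounder is to be recognised, or whether the bands are tested separately or combined.
- **Effect sizes.** Cohen's d is calculated before and after the intervention, and the first is subtracted from the second to control for baseline differences. No test or interval is attached to the result.
- **Significance.** "Differences will be considered statistically significant when *p* < 0.05".
- **Size and allocation.** From Sample Size Calculation: "considering a 10% attrition rate, the total sample size will be 44 participants", and "Each group had 22 participants". From Allocation Sequence Generation: "The participants will be randomly allocated at a 1:1 ratio" by an online tool. No stratification is described.

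**The concern.** When allocation is properly randomised, any baseline difference is a chance difference, so a baseline p-value tests a hypothesis already known to be true. A non-significant result in a small trial is weak evidence of balance. The question that matters is whether an imbalance in a prognostic variable is large enough to shift the treatment comparison, and a p-value does not answer it.

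This has consequences here because the between-group test takes no account of baseline. An imbalance in the baseline outcome that goes unremarked carries straight into the post-intervention difference. For age, the stated response would divide a trial of 44 into three parts instead of using all patients for one age-adjusted estimate. Both the baseline outcomes and age are already collected, so the information needed for a better analysis is at hand.

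**Working it through.** **Inputs from the article.** 44 patients, 22 per arm, 1:1, 10% attrition, significance at 0.05 (two-sided assumed, as sidedness is not stated), three age bands.

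**Assumptions, not in the article.** Baseline–outcome correlation r of 0.5 to 0.8; treatment effect d = 0.8 for illustration; the age distribution.

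**1. The plan's own figure.** No effect size, SD or power is given, so 44 cannot be derived. Only the attrition step can be checked. 44 × 0.9 = 39.6, about 40 evaluable or 20 per arm. Conversely, 40 × 1.10 = 44, and 39 / 0.9 = 43.3, rounded up to 44. About 40 evaluable patients is consistent with the text.

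**2. What a non-significant baseline test allows.** The smallest observed difference reaching p < 0.05, in SD units, is t(0.975, 42) × √(2/22) = 0.608. For true shifts, the power of the two-sample t-test at 22 per arm is:

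| Shift (SD) | Power |
|---|---|
| 0.3 | 16% |
| 0.5 | 37% |
| 0.8 | 74% |
| 1.0 | 90% |

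By chance alone, an imbalance of 0.3 SD or more in a given variable arises in 2 × [1 − Φ(0.3 / √(2/22))] = 32% of randomisations, and one of 0.5 SD or more in about 10%.

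**3. What such an imbalance does to the unadjusted test.** With a baseline imbalance δ and correlation r, the expected shift in the post-intervention difference is r × δ. For δ = 0.5 SD this is 0.5 × 0.5 = 0.25 SD up to 0.8 × 0.5 = 0.40 SD with no treatment effect at all. Simulated rejection rates under no treatment effect (22 per arm, 6,000 runs per setting):

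| Imbalance | r | Post-value t-test | ANCOVA on baseline |
|---|---|---|---|
| 0.3 SD | 0.5 | 4.6% | 5.1% |
| 0.3 SD | 0.7 | 4.1% | 5.2% |
| 0.3 SD | 0.8 | 2.6% | 5.1% |
| 0.5 SD | 0.5 | 9.6% | 5.2% |
| 0.5 SD | 0.7 | 13.1% | 4.9% |
| 0.5 SD | 0.8 | 13.9% | 5.1% |

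The unadjusted test is conservative at small imbalances and liberal at larger ones. An observed imbalance of 0.5 SD lies below the 0.61 SD threshold and would be reported as no significant difference.

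**4. Precision.** Adjustment for baseline turns d into d / √(1 − r²), ignoring the small loss of degrees of freedom. For d = 0.8 and 20 per arm, power is 69% for the post-value t-test, against about 81% (r = 0.5), 93% (r = 0.7) or 98% (r = 0.8) for ANCOVA.

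**5. The age bands, read as separate tests.** An even split gives 22 / 3 = 7.3 per arm per band as randomised, or 20 / 3 = 6.7 after attrition.

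| Per arm per band | Power at d = 0.8 | d for 80% power |
|---|---|---|
| 7 | 28% | 1.63 |
| 6 | 24% | 1.80 |

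Three tests at 0.05 have a family-wise error of 1 − 0.95³ = 14.3%. If only 10% of patients were aged 18–30, the chance that at least one arm has fewer than two of them is about 56%; at 5% it is about 91%.

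**The case against.** Several stronger readings are tempting, and the article does not support them.

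- **That the baseline tests act as a gate.** Nothing makes the main comparison conditional on a baseline p-value. Nor does the text say that such a p-value sets off the age analysis; it leaves the trigger undefined.
- **That nothing is done about baseline differences except through age.** The effect-size subtraction is planned for all outcomes and is unconditional. It partly corrects baseline imbalance in the outcome. It remains a descriptive figure that does not enter the between-group test and does not deal with age.
- **That the tests and the bands are useless.** The tests have 90% power at 1.0 SD, and banding removes part of the confounding by age. They are unreliable and inefficient, not without effect.
- **That chance findings at baseline will produce unplanned subgroups.** There are about 18 baseline comparisons (5 descriptors and, by count, 13 outcomes), so the chance of at least one p < 0.05 is 1 − 0.95¹⁸ = 60% if they were independent. Walking measures, for example, are unlikely to be independent, so the true figure would be lower. It also has no bearing on the age remedy: a chance flag on age itself has probability 5%. The bands are named in advance and labelled secondary; only the decision to use them is open.
- **That the bands must mean three separate tests.** The wording could also cover age group as a stratifying factor. The power figures for the bands hold only on the separate-tests reading with an even split.

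It is also fair to say that the article gives no evidence that age is prognostic in this population. Age is proposed as a covariate because it is the variable the plan itself singles out.

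What stands is a weakness in methods that the article states outright, so it is not a detail left to a separate analysis plan.

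**Conclusion.** The point holds in a limited form. Tests at 22 per arm that leave observed imbalances up to about 0.61 SD non-significant cannot ensure comparability. The between-group test is unadjusted, and the only stated response to confounding by age has no rule for when it applies and, if run as separate tests, would have 24–28% power per band at d = 0.8, with less in a sparse band.

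A reader might infer that the trial's false-positive rate is inflated. It is not, on average over randomisations: proper randomisation protects the unconditional type I error. The 9.6–13.9% rejection rates apply conditionally on a 0.5 SD imbalance and on the assumed r of 0.5 to 0.8. What the plan forgoes is precision and protection against conditional bias in the one randomisation that occurs. Because the remedy uses data already collected, the change is worth making even though the present analysis is not invalid.

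**What to change.** 1. Remove the baseline hypothesis tests and present baseline characteristics descriptively by arm, without p-values.
2. Pre-specify the between-group analysis as ANCOVA on the post-intervention value, with the baseline value of the same outcome and age as a continuous covariate, whatever imbalance is observed. For MAS and MMT, use an ordinal model with the same covariates.
3. Drop the three-band age analysis, or show band summaries descriptively without p-values.

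The cost is analysis wording and two degrees of freedom compared with the t-test: with 40 evaluable patients, residual degrees of freedom go from 40 − 2 = 38 to 40 − 4 = 36. No additional patients, visits or measurements are needed.

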#### Inclusion Criteria

Participants will be included if they had a first incident of brain stroke aged from 18 to 65 years old and have at least 6 months since stroke to avoid the effects of spontaneous recovery. Independent ambulatory ability with or without assistive device at least 10 m (e.g., cane and walker), plantarflexors spasticity on paretic limb ≥2 on modified Ashworth scale (MAS) (12), and functional ambulation ≥3 on functional ambulation categories (13).

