### Outcome Measures

Primary and secondary outcome measures will be collected by a blinded trained assessor at the baseline and after the intervention (4 weeks of intervention). Primary outcomes will include spasticity in the plantarflexor muscles in paretic leg measured by MAS, active and passive ROM for the ankle joint in paretic leg measured by a handheld goniometer, muscle strength for the ankle dorsiflexor muscle in paretic leg measured by manual muscle testing (MMT), gait speed using 10-meter walk test (10-MWT). Secondary outcome measures will include mobility function using Timed Up and Go (TUG), walking endurance using 6 MWT, ADL using the Arabic version Barthel index (BI), and self-reported health measures such as Medical Outcomes Survey (Short Form-36, SF-36), physical activity using RAPA, depression symptoms using Patient Health Questionnaire-9 (PHQ-9), fatigue level using the Arabic version of Fatigue Severity Scale (FSS), and risk of fall using the Arabic version of Fall Efficacy Scale International (FES-I).

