##### Modified Ashworth Scale

The spasticity in the plantarflexor muscles tone will be measured on the affected leg using MAS. Participants will be placed in a supine position. To test ankle plantarflexor muscles' spasticity, from maximal ankle plantarflexor position, the assessor passively moves the ankle to maximal dorsiflexion position over 1 s. The test will be performed at the baseline and post-intervention. Spasticity will be graded according to MAS, which is a 6-point rating scale (12):

0 No increase in muscle tone.1 Slight increase in muscle tone, manifested by a catch and release or by minimal resistance at the end of the ROM when the affected part(s) is moved in flexion or extension.1+ Slight increase in muscle tone, manifested by a catch, followed by minimal resistance throughout the remainder (less than half) of the ROM.2 More marked increase in muscle tone through most of the ROM, but affected part(s) easily moved.3 Considerable increase in muscle tone, passive movement difficult.4 Affected part(s) rigid in flexion or extension.

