##### Manual Muscle Testing for Ankle Dorsiflexors

In clinical practice, muscle strength is most often evaluated using the manual muscle strength testing of the Medical Research Council (MRC) grade. The ankle dorsiflexor strength will be graded according to the (MMT; graded from 0 (no contraction at all) to 5 (full range of movement against power and the same force as on the opposite side) for ankle dorsiflexor. The test will be performed at the baseline and post-intervention. To perform the test, the participant will be in short sitting with ankle plantarflexed. The assessor will be in front of the participant sitting using one hand to stabilize the leg just above the malleoli. The other hand will provide the resistance to the dorsal aspect of the foot. A participant will be asked to dorsiflex his/her ankle actively against the resistance (14).

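### The ordinal primary outcomes MAS and MMT go through a normality check and are summarised by Cohen's d, which treats grades as interval and, for MAS, depends on the number given to grade 1+

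*Protocol article*

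**What the plan says.** Under Outcome Measures, both scales are primary: "Primary outcomes will include spasticity in the plantarflexor muscles in paretic leg measured by MAS", and "muscle strength for the ankle dorsiflexor muscle in paretic leg measured by manual muscle testing (MMT").

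Both are ordered grades. Under Modified Ashworth Scale: "Spasticity will be graded according to MAS, which is a 6-point rating scale", with grades 0, 1, 1+, 2, 3 and 4. Grade 1+ is defined only in words ("1+ Slight increase in muscle tone, manifested by a catch, followed by minimal resistance throughout the remainder") and is given no number. Under Manual Muscle Testing for Ankle Dorsiflexors, strength is "graded from 0 (no contraction at all) to 5 (full range of movement against power").

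The Inclusion Criteria require "plantarflexors spasticity on paretic limb ≥2 on modified Ashworth scale (MAS").

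The Statistical Analysis section makes no exception for ordinal scales:
- "Normality of the data will be assessed using the Shapiro–Wilk test".
- Within groups, a paired t-test or Wilcoxon signed rank test is used. Between groups, an independent t-test or Mann–Whitney test is used on post-intervention values.
- Cohen's d is calculated for the outcome measures. The pre-test d is subtracted from the post-test d, and 0.8 or more is labelled large.

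The Abstract names only the independent t-test.

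**The concern.** Cohen's d is a difference in means divided by a standard deviation. For MAS and MMT it assumes that each step between grades is worth a known amount, which an ordinal scale does not supply. For MAS it cannot be computed at all until 1+ is given a number, and 1.5 on a 0–4 code or 2 on a 0–5 code are both natural choices. The step from grade 2 to 1+ is the smallest improvement available to a patient who enters at grade 2, so the uncertain value sits where a treatment effect would show.

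A normality test is also a poor basis for choosing a method here, because data confined to a few grades are not normal whatever the treatment does.

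At stake is how the effect on two primary outcomes is reported. The p-value would probably come from a rank test, while the effect size and its label would come from a mean on an unstated code.

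**Working it through.** **Inputs.** The grades, the entry rule, the tests and the 0.8 threshold are in the article. So are 44 patients and 10% attrition, giving 44 × 0.9 = 39.6, or about 20 per arm. The article gives no MAS or MMT distributions, so all counts below are assumptions. No stated figure bears on this point, so there is none to reproduce.

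**Formula.** d = (mean sham − mean active) / √[(s₁² + s₂²)/2]. Positive values favour active stimulation.

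**One pattern in full (pattern B).** Post-intervention counts for grades 0/1/1+/2/3/4 are 0, 1, 9, 8, 2, 0 (active) and 0, 0, 3, 11, 5, 1 (sham).

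| Code | Mean active | Mean sham | Pooled SD | d | t-test p | Mann–Whitney p |
|---|---|---|---|---|---|---|
| 1+ = 1.5 | 36.5/20 = 1.825 | 45.5/20 = 2.275 | 0.582 | 0.450/0.582 = 0.77 | 0.019 | 0.013 |
| ranks 0–5 | 51/20 = 2.55 | 64/20 = 3.20 | 0.763 | 0.65/0.763 = 0.85 | 0.010 | 0.013 |
| 1+ merged with 1 | 32/20 = 1.60 | 44/20 = 2.20 | 0.725 | 0.60/0.725 = 0.83 | 0.013 | 0.015 |

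The first two codes preserve the order of the grades, and the Mann–Whitney p is identical under them. So is the probability of superiority. Of the 400 pairs, the active patient has the lower grade in 20 + 153 + 48 + 2 = 223 and ties in 27 + 88 + 10 = 125, so (223 + 62.5)/400 = 0.71.

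**All five patterns.** Counts are for grades 0/1/1+/2/3/4, 20 per arm.

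| Pattern | Active | Sham | d: 1.5 / ranks / merged | Range |
|---|---|---|---|---|
| A | 0,3,7,8,2,0 | 0,0,4,11,5,0 | 0.69 / 0.76 / 0.66 | 0.10 |
| B | 0,1,9,8,2,0 | 0,0,3,11,5,1 | 0.77 / 0.85 / 0.83 | 0.08 |
| C | 0,2,5,9,3,1 | 0,1,3,10,5,1 | 0.28 / 0.31 / 0.30 | 0.03 |
| D | 0,0,14,6,0,0 | 0,0,6,12,2,0 | 0.87 / 0.91 / 0.91 | 0.04 |
| E | 2,6,6,5,1,0 | 0,2,4,9,5,0 | 0.96 / 0.99 / 0.95 | 0.04 |

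A sixth pattern has active 10/50/30/10% and sham 10/10/60/20% in grades 1/1+/2/3. It gives a d of size 0.555 with 1+ = 1.5 and 0.613 with ranks. Merging 1+ with 1 gives means 1.5 and 2.0 and variances 0.45 and 0.40, so 0.5/√0.425 = 0.77. That range is 0.21, the widest seen.

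**Baseline and the subtraction.** Taking the baseline grade to satisfy the entry rule, only grades 2, 3 and 4 occur at T0, so 1+ is absent. With assumed counts for grades 2/3/4 of 12, 7, 1 (active) and 10, 8, 2 (sham), d = 0.15/√[(0.366 + 0.463)/2] = 0.233 under all three codes. Subtraction removes none of the coding effect. In pattern B the difference is 0.77 − 0.23 = 0.54 or 0.85 − 0.23 = 0.62, the same 0.08 apart. Here neither value reaches 0.8. The label changes for the post-test d, or for the difference if the arms are balanced at baseline.

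**What the normality check does.** Over patterns A to E, Shapiro–Wilk rejected in at least one arm in 97–100% of simulated MAS trials. For MMT, under one assumed distribution, the figure was about 92%.

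**The case against.** Much of the opposing case stands.

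- **The switch is not written down.** The article says that normality will be assessed and then names two tests. Choosing by scale type is not excluded and could be in an unseen analysis plan. The routing is an inference from the order of the sentences.
- **A reader might infer that the spasticity test is decided by noise.** The simulations do not support this. Under patterns A to E the check leads almost always to Mann–Whitney. Under four further assumed MAS distributions both arms passed in only 0–21% of trials.
- **A reader might infer that the effect grows by two thirds with the code,** because the raw difference in the sixth pattern goes from 0.30 to 0.50. That is mostly a change of units. The planned measure is standardised, and 0.613/0.555 is about 1.10. The 0.06 shift is under one fifth of the simulated sampling SD of d, about 0.35 at 20 per arm.
- **A reader might infer that Mann–Whitney leaves no effect estimate.** That is wrong, since Cohen's d is planned whichever test is used. The t-test on post-intervention values is equally unadjusted for baseline.
- **Spasticity cannot be called the lead outcome.** The primary outcomes carry no ranking.
- **The 1+ problem is confined to MAS.** MMT grades are numeric. A missing code alone is also a detail that an article may leave to an analysis plan.

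What remains is what the article itself fixes: a normality check and Cohen's d for all outcome measures, including two ordinal ones.

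**Conclusion.** The point holds as a mismatch between scale and summary, with limited numerical effect. For MAS and MMT, the normality check does no useful work, and Cohen's d treats the grades as interval. For MAS alone, d also depends on the code for 1+, and all of that dependence passes into the post-minus-pre d.

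Under assumed distributions the shift in d is about 0.03 to 0.10 in five of six patterns. It can move a result across the 0.8 threshold, as in pattern B. The Mann–Whitney p-value is untouched by any order-preserving code, so the documents do not support a claim that the between-group finding on spasticity would generally turn on coding. It would do so only if the t-test were used, as the Abstract suggests. In pattern A the t-test p is 0.036, 0.022 or 0.044 under the three codes, all below 0.05. The sizes rest wholly on assumed counts at about 20 per arm.

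**What to change.** Change the analysis wording for MAS and MMT only:

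1. Drop the normality check for these two outcomes.
2. Pre-specify an ordinal analysis of the post-intervention grade that uses the baseline grade. One example is a proportional-odds model reporting the common odds ratio with its 95% CI, with a rule for merging sparse grades (such as 3 with 4) stated in advance.
3. Support it with Mann–Whitney and the probability of superiority with its 95% CI.
4. Tabulate the post-intervention grades by arm.
5. Do not report Cohen's d for these outcomes. If any mean-based summary is kept, fix the number for 1+ before unblinding.
6. Bring the Abstract's single t-test into line.

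No extra patients, visits or measurements are needed, since baseline grade is already collected. The cost is one added assumption, proportional odds, which about 20 patients per arm can check only weakly, and some loss of detail if grades are merged. Entering baseline grade as a numeric score would bring equal spacing back for the covariate. For MAS this is easily avoided, because the entry rule leaves only three baseline grades, which can be entered as categories.

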## Abstract

**Introduction:** Rehabilitation approaches have been used for people with stroke to decrease spasticity and improve functions, but little is known about the effect of neuromuscular electrical stimulation (NMES) in this population. Therefore, the primary purpose of this study was to establish a protocol for a double-blinded randomized clinical trial to examine using NMES on plantarflexors spasticity, dorsiflexor muscle strength, physical functions, and self-reported health outcomes in people with chronic stroke in Saudi Arabia.

**Material and Methods:** This randomized clinical trial with two arms and double-blinded registered in ClinicalTrials (NCT04673045) will enroll 44 participants with chronic stroke and randomized them into either the experimental group (EG), including electrical stimulation (ES) with conventional therapy or the control sham group (NMES_sham_) including placebo electrical stimulation with conventional therapy. The frequency will be set at 80 Hz for 30 min. The intervention will be three times a week for 4 weeks for both groups. Data collection for pre- and post-intervention outcomes will include measurements for the primary outcomes including paretic limb (plantarflexor spasticity, ankle range of motion, and dorsiflexor muscles strength), and gait speed using 10-m walk test (10-MWT). The secondary outcomes including mobility function using Timed Up and Go (TUG), walking endurance using 6 Minutes Walk Test (6-MWT), activity of daily living using the Arabic version of Barthel Index (BI), and self-reported health measures such as quality of life using the Medical Outcomes Survey (Short Form 36, SF-36), physical activity using Rapid Assessment of Physical Activity (RAPA), depression symptoms using Patient Health Questionnaire-9 (PHQ-9), fatigue level using Fatigue Severity Scale (FSS), and risk of fall using Fall Efficacy Scale International (FES-I). An independent *t*-test will be utilized to examine the effect of the intervention on the outcome measures.

**Results:** The recruitment has started and is ongoing.

**Conclusions:** Using 4 weeks of NMES will provide information about its effect in improving plantarflexor spasticity, dorsiflexor muscles strength, gait speed, mobility functions, and other self-reported health outcomes in people with chronic stroke when compared to NMES_sham_.

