## Discussion

The main objective of this clinical trial is to evaluate the effect of using NMES on plantarflexor muscle spasticity, ankle ROM, dorsiflexor muscle strength, and gait speed. The secondary objective of this work is to examine the effect of using NMES on mobility function, walking endurance, and self-reported outcomes such as ADL, QoL, physical activity, depression symptoms, fatigue level, and risk of fall.

The findings from this study will highlight the importance and effect of using electrical stimulation during a rehabilitation program for individuals with chronic stroke living in Saudi Arabia. If the findings are positive, this study will be the first that has preliminary positive results for a rehabilitation program using NMES in this population in Saudi Arabia. The results will eventually help healthcare providers and other researchers in choosing and investigating the appropriate rehabilitation approach to improve spasticity and functionality.

Upon completion of data collection, it is expected that the active NMES group will benefit from decreased ankle plantarflexors spasticity, increased dorsiflexors strength, and improved walking function, physical activity, and QoL. The placebo group will gain benefit from CRP; however, it is expected that the scores of placebo group in targeted outcomes will show less variation than EG. The result will be published after the data and the study is completed.

Although this study has some strengths including blinded assessors, blinded participants, and placebo NMES to decrease bias, there are some limitations. A single center study is a possible limitation that may limit the generalizability of the results. Using a clinical setting (hospital outpatient clinic) with lack of tools is another limitation that may limit the use of objective tools such as EMG. Drop out is another limitation that may occur in clinical trials that affects sample size and results. Lack of follow-up assessment after the intervention is another limitation due to limited financial resources that affect the results of long-term effect and persistence of the results of this treatment.

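### Within-arm pre-post significance tests are planned at the same p < 0.05 rule as the between-arm test, although they cannot isolate an NMES effect

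*Protocol article*

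**What the plan says.** The Statistical Analysis section lists two sets of tests.

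- **Within each arm:** "Comparisons between pre- and post-intervention will be conducted using the dependent *t*-test or the Wilcoxon signed rank test", with the stated purpose "to determine if there will be significant differences between two different timepoints for each group".
- **Between arms:** "The independent *t*-test or the Mann–Whitney *U*-test will be used to compare the recorded values at the post-intervention between the two groups".

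One rule covers both sets: "Differences will be considered statistically significant when *p* < 0.05". Nothing labels the within-arm tests descriptive or secondary to the between-arm test. The section also plans Cohen's d between the groups, with the pre-test value subtracted from the post-test value, but names no test for that difference. The Abstract is clearer about which comparison carries the treatment effect: "An independent *t*-test will be utilized to examine the effect of the intervention on the outcome measures".

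Three other statements bear on the point. The Intervention section gives all participants the same rehabilitation programme, three times a week for 4 weeks. The Discussion expects the placebo group to gain from that programme and adds that "it is expected that the scores of placebo group in targeted outcomes will show less variation than EG". Inclusion Criteria require a plantarflexor MAS grade of 2 or more on the paretic side, and MAS is also an endpoint: "Primary outcomes will include spasticity in the plantarflexor muscles in paretic leg measured by MAS".

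**The concern.** A paired test asks whether an arm changed between T0 and T1. In this trial the answer may well be yes in both arms whether or not NMES works, because both receive active rehabilitation and the authors expect it to help. Expectation and attention effects, which the Introduction gives as the reason for a sham arm, also stay inside a within-arm change. The criterion of at least 6 months since stroke deals with spontaneous recovery only.

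The hazard lies in setting the two p-values side by side. If the active arm reaches p < 0.05 and the sham arm does not, it is easy to write that NMES improved the outcome and sham did not. That conclusion does not follow, because the difference between the arms has not been tested by that comparison. The layout of the plan makes the misreading easier. Study Design describes a group factor and a time factor, but the analysis tests no group-by-time contrast, so the within-arm tests are the only significance tests of change in the plan.

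**Working it through.** **Inputs from the protocol article.** 22 per arm and 1:1 allocation (Allocation Sequence Generation); 10% attrition (Sample Size Calculation); significance at 0.05 (Statistical Analysis); rehabilitation three times a week for 4 weeks in both arms (Intervention), so 3 × 4 = 12 sessions.

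**Assumptions.** Tests are two-sided. Both arms share the same true mean change, δ, in units of the SD of the change scores, and NMES adds nothing. The document gives no value for δ, so a range is shown.

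**Step 1: number of within-arm tests.** The primary outcomes are MAS, active ROM, passive ROM, MMT and 10-MWT (5). The secondary outcomes are TUG, 6-MWT, Barthel Index, SF-36, RAPA, PHQ-9, FSS and FES-I (8). 5 + 8 = 13 outcomes, and 13 × 2 arms = 26 tests. Testing SF-36 subscales separately would raise the count.

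**Step 2: patients per arm.** The plan states no power or error rate for these tests, so there is no such figure to reproduce. Its total of 44 agrees with an assumed 40 × 1.1 = 44, but the base number cannot be rederived because no effect size, SD or power is given. With 10% attrition, 22 × 0.9 = 19.8, or about 20 per arm.

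**Step 3: how often only the active arm is significant.** For a paired t-test with n patients, the chance of a significant improvement is p = P(T > t), where t is the 0.975 quantile of the t distribution on n − 1 degrees of freedom and T is noncentral t with noncentrality δ√n. The arms are independent, so:

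- active arm only: p(1 − p)
- exactly one arm: 2p(1 − p)
- at least one arm: 1 − (1 − p)²

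For n = 20 and δ = 0.5, the noncentrality is 0.5 × √20 = 2.236 and p = 0.564. Active arm only is 0.564 × 0.436 = 0.246.

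| n per arm | δ | p, given arm | active arm only | exactly one arm | at least one arm |
|---|---|---|---|---|---|
| 20 | 0.3 | 0.246 | 0.186 | 0.371 | 0.432 |
| 20 | 0.44 | 0.463 | 0.249 | 0.497 | 0.712 |
| 20 | 0.5 | 0.564 | 0.246 | 0.492 | 0.810 |
| 20 | 0.6 | 0.721 | 0.201 | 0.402 | 0.922 |
| 20 | 0.8 | 0.924 | 0.070 | 0.141 | 0.994 |
| 22 | 0.5 | 0.609 | 0.238 | 0.476 | 0.847 |

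The function p(1 − p) cannot exceed 0.25, reached at p = 0.5. The figure falls on either side: at 20 per arm it is 0.116 for δ = 0.2, and 0.024 when there is no common change at all.

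**Step 4: the comparator.** With no NMES effect, the between-arm test is significant about 5% of the time per outcome. Half of that, about 2.5%, favours the active arm.

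**Step 5: an added mechanism for MAS only.** Patients enter on a high MAS grade. If that reading also serves as baseline, and MAS is measured with error, the next reading tends to be lower with no true change. A simulation used a latent normal tone score cut into six grades at assumed points, entry at grade 2 or more, 20 per arm and 2,000 trials per setting. With no true change, a paired t-test showed a significant fall in a given arm in 0% of trials at reliability 1.0, 22% at 0.9, 40% at 0.8, 51% at 0.7 and 78% at 0.5. Over all settings run, including those with a true change common to both arms, the between-arm test of T1 values was significant in 3.7% to 6.2% of trials, close to its nominal 5%.

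**The case against.** The strongest reply is that the plan does not say it will draw a conclusion about NMES from the paired tests. Their stated purpose is to compare two timepoints within each group. The Abstract ties the effect of the intervention to the independent t-test, and the Statistical Analysis section plans that test. This stands, and it limits the point. A reader might infer that the trial gives up the benefit of its sham control. The documents do not support that: the randomised comparison is planned and its error rate is not affected.

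The Discussion sentence about less variation in the placebo group can also be over-read. It is an expectation about results, not an analysis rule, and the same sentence expects the placebo group to improve.

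A third tempting reading is that entry on a high MAS grade will produce apparent improvement across the outcomes. That is too strong. The entry threshold acts directly on MAS alone. The size of the effect depends on MAS reliability, which is not given, and on whether the screening reading is also the baseline reading, which is not stated. The Intervention section describes screening and a pre-training assessment within 3 days before training, so they could be separate readings, and the effect would then be smaller.

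Finally, 25% is the mathematical ceiling for the active-only pattern, not a typical value. With a large common change both arms tend to be significant, and the pattern becomes uncommon.

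These replies do not change the fact that two sets of tests share one significance rule and only one of them bears on NMES.

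**Conclusion.** The point holds as a risk of misleading parallel evidence. The plan sets 26 or more within-arm tests beside the between-arm test under one 0.05 rule, with no order of importance, in a trial where both arms are treated and the sham arm is expected to improve.

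If NMES has no effect, significance in the active arm only would arise for a given outcome in about 7% to 25% of trials, assuming a common change of 0.3 to 0.8 SD of the change scores, 20 per arm and a paired t-test. The between-arm test would be significant about 5% of the time (two-sided). Regression to the mean can add to this for MAS, by an amount the document does not allow anyone to fix. The main argument rests on the shared rehabilitation and does not need it.

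This should be corrected before analysis, but it does not undermine the design.

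**What to change.** In the Statistical Analysis section, replace the dependent t-test and the Wilcoxon signed-rank test with a descriptive report of within-arm change for each outcome: mean or median change with a 95% CI and no p-value. Add a sentence stating that every claim about NMES rests on the between-group contrast at T1, adjusted for the baseline value of the same outcome, for example ANCOVA for continuous outcomes and an ordinal model for MAS and MMT.

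The baseline values are already collected, so no new data are needed. The cost is a small added analysis, because the plan at present has only an unadjusted test of post-intervention values and a subtraction of effect sizes.
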